**Exploratory endpoints:**

- S2.EE1 The proportion of patients with a reduction of >25% in haemoglobin to a concentration of < 7 g/dl

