| 9.0     | -deletion of exploratory analysis for haemoglobin change (S2.EE1 absolute & S2.EE2 proportional in the first 3 days) as haemoglobin data only routinely collected at baseline in Stage 2.

-addition of subgroup of Sumatra compared to PNG & Indonesian Papua.

-sensitivity analysis of S2.SE15 changed from pre-implementation period of 3 years (data not available across all clinics) to including only incidence data from previous 12 months. | 11-NOV-2025 |

|  |                                                                                                                                                                                                                                                                                                                                                                                                                                                                                                                                                                                                                                                                                                                                                                              |  |
|--|------------------------------------------------------------------------------------------------------------------------------------------------------------------------------------------------------------------------------------------------------------------------------------------------------------------------------------------------------------------------------------------------------------------------------------------------------------------------------------------------------------------------------------------------------------------------------------------------------------------------------------------------------------------------------------------------------------------------------------------------------------------------------|--|

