### 3.1.2. Stage 2 – Large-scale implementation and feasibility study

Stage 2 of the study will be a feasibility study conducted at 10 community health-care facilities: 6 sites in Indonesia and 4 sites in Papua New Guinea. The primary purpose of Stage 2 is to determine the feasibility and cost-effectiveness of the complete revised case management initially studied in Stage 1. Robust Pre-Implementation malarimetric surveillance for a minimum of 12 months along with quantitative surveys of baseline operational metrics and costs will be followed by coordinated introduction of the revised case management across all study health facilities and a minimum of a further 12 months of surveillance – creating an interrupted time series comparing the endpoints listed in section 2.2.2.

During Stage 2 study procedures will be the same as those for Stage 1, except that the procedures will be performed by routine healthcare staff. All patients will be reviewed by community health workers (CHW) at home 3 days after starting PQ. The review may also take place at the health facility, if the patient presents there. Exceptionally, the follow-up may also take place via a phone call if the patient is not physically reachable at home. The CHW will complete a signs and symptom checklist to detect early indicators of haemolysis or other AESI. Patients with signs of haemolysis or other AESI will have their primaquine ceased and will be referred to the health facility for medical review. Patients tolerating their medication will be encouraged to adhere to a full (7 or 14 days) course of treatment. Safety outcomes occurring between day 3 and end of treatment will be detected passively by community-based health workers, study health facilities and regional hospitals.

Continuous surveillance and pharmacovigilance over the entire study period will enable interrupted time-series analyses of malarimetric indices (see section 2.2.2).

Figure 1 presents the study schedule for the baseline data, pre-implementation stage, and stages 1 and 2.

**Figure 1. Study overview**[figure not shown]

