## 8 Handling of Missing Values

We do not expect there to be any reason that calendar time month will be missing for any observations over the study period (pre-implementation, Stage 1 and Stage 2) at each of the 10 sites. This is based on our experience of routine data collection during the baseline data period (i.e. prior to pre-implementation stage). We will descriptively report the patterns of missingness for the outcome measures and other participant variables over time in each site. For all analyses, missing data will be handled using an available case analysis, i.e. missing data on any variable included in the analysis where the observation for an individual at that time point is missing is excluded from the analysis.

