Individual patient data on the risk of representation with vivax malaria within 6 months to the same health facility site (S2.SE17) will be analysed using survival analysis and visualised with Kaplan-Meier curves. The risk of recurrence will be determined for all patients eligible for PQ treatment and compared between the pre- and post-implementation stages. Multivariable Cox proportional hazards regression will be used to compare these same groups, controlling for age, sex, body weight, calendar time (month), seasonality (captured using splines) and shared frailty of health facility. The validity of the proportional hazards assumption will be assessed visually using Schoenfeld residuals and stratified analyses will be conducted where the assumption is violated.

For S2.EE1, the number and proportion (and 95% Confidence Interval) of patients observed to have a >25% reduction in haemoglobin to a concentration below 7 g/dl will be computed by treatment arm (PQ7, PQ14, PQ8w), and described in summary tables.

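### Exploratory endpoint S2.EE1 needs a follow-up haemoglobin that Stage 2 does not routinely collect, and the SAP does not fix its denominator

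*SAP*

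**What the plan says.** Section 2.2.2 lists one exploratory endpoint for Stage 2, S2.EE1: "The proportion of patients with a reduction of >25% in haemoglobin to a concentration of < 7 g/dl". It names no denominator and no time window. The analysis is in Section 9.2: "For S2.EE1, the number and proportion (and 95% Confidence Interval) of patients observed to have a >25% reduction in haemoglobin", to below 7 g/dl, computed for PQ7, PQ14 and PQ8W and shown in summary tables.

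The version 9.0 entry in the SAP Revision History removes the absolute and proportional haemoglobin-change endpoints from Stage 2, "as haemoglobin data only routinely collected at baseline in Stage 2".

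Section 3.1.2 describes the Stage 2 day-3 contact: "The CHW will complete a signs and symptom checklist to detect early indicators of haemolysis or other AESI". It may exceptionally be made by telephone. What follows is triggered by symptoms: "Patients with signs of haemolysis or other AESI will have their primaquine ceased and will be referred to the health facility for medical review". After day 3, detection of safety outcomes is passive.

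Section 8 sets one rule for missing values: "For all analyses, missing data will be handled using an available case analysis".

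**The concern.** The retained endpoint depends on the same follow-up value whose absence led to the deletion of its two sister endpoints. The SAP does not say how a patient without that value is to be counted. Two analysts could follow the text faithfully and report very different proportions from the same data, each with a 95% confidence interval that conveys only sampling error.

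At stake is the reading of one table. A proportion based mainly on patients re-tested for symptoms could be taken as the risk in everyone treated. A minimum could be taken as an estimate. Differences between the three regimen columns could reflect who was re-tested: the single scheduled contact on day 3 covers a different share of a 7-day, a 14-day and an 8-week course.

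**Working it through.** **Plan's own figure.** The SAP states no expected rate or precision for S2.EE1, so there is nothing to reproduce. The nearest stated figure is under S2.SE9 in Section 4.2.1 (1% with a half-width of 0.18% at 11,410 patients). Check: 1.96 × √(0.01 × 0.99 / 11,410) = 0.00183, or 0.18%. It agrees, so 11,410 is used below as the planned number treated.

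**Step 1: can baseline data alone show the event?** No. Section 3.2 requires haemoglobin of at least 8 g/dl at entry, and the event needs a value below 7 g/dl. A later measurement is indispensable for any eligible patient.

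**Step 2: who has a later measurement?**
- It is not routine in Stage 2 (Revision History, version 9.0).
- The day-3 contact is a symptom checklist. Patients with signs are referred, and S2.SE7 sends flagged patients to level 2 review (Sections 2.2.2 and 3.1.2).
- In Appendix 1, post-baseline haemoglobin fields appear on the Level 2, Level 3 and SAE forms.

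It follows, as an inference and not as a stated fact, that follow-up values will come mainly from symptomatic patients.

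**Step 3: the two readings.** Let N be the number treated, R the number with a follow-up haemoglobin and x the number of observed events.
- Available case: x / R.
- All treated: x / N.
- Ratio of the two: (x / R) / (x / N) = N / R, the reciprocal of the re-tested share. The number of events cancels.

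For illustration, take x = 20 (assumed) and N = 11,410. The shares are also assumed, and the intervals are exact binomial.

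| Re-tested share | R | x / R (95% CI) | Ratio to x / N |
|---|---|---|---|
| 100% | 11,410 | 0.18% (0.11–0.27) | 1 |
| 20% | 2,282 | 0.88% (0.54–1.35) | 5 |
| 10% | 1,141 | 1.75% (1.07–2.69) | 10 |
| 5% | 570 | 3.51% (2.16–5.37) | 20 |
| 2% | 228 | 8.77% (5.44–13.22) | 50 |

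At a 3% share the ratio is 1 / 0.03 = 33.

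**Step 4: does either reading recover the true risk?** Assume a true risk of 0.3%, with 60% of true events and 5% of non-events re-tested.
- True events: 11,410 × 0.003 = 34.2. Observed events: 34.2 × 0.6 = 20.5.
- Re-tested: 20.5 + (11,410 − 34.2) × 0.05 = 20.5 + 568.8 = 589.
- Available case: 20.5 / 589 = 3.48%. All treated: 20.5 / 11,410 = 0.18%.

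The first is too high and the second too low against 0.3%. The direction of the available-case error rests on events being re-tested more often than non-events, which the pathway in Step 2 makes likely.

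**The case against.** Several points on the other side stand.

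- **The endpoint is minor.** S2.EE1 is exploratory, and no sample size or decision rule uses it. A reader might infer that Stage 2 lacks a sound haematological safety measure. The SAP does not support that: S2.SE11 (haemolysis AESI) and S2.SE14 (severe anaemia in the surveys) are listed secondary endpoints and do not rest on this proportion.
- **Section 9.2 already reports the number as well as the proportion.** It speaks of patients observed to have the fall, which hints at detected cases. S2.SE10 to S2.SE13 use primaquine-treated patients as denominator, a natural reading here too. Inflation through the available-case rule is therefore conditional, not certain. Section 8 refers to observations missing at a time point, and S2.EE1 has none. Even so, the rule is written for all analyses and nothing exempts S2.EE1.
- **Incomplete detection is openly part of the design.** It touches the other Stage 2 safety endpoints as well. That does not make an unlabelled minimum harmless.
- **Section 3.1.2 says that Stage 2 procedures match those of Stage 1 apart from staffing.** This could suggest a day-3 haemoglobin. The same section describes only a checklist, and the Revision History says explicitly that routine collection is at baseline.

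Three further inferences go too far. The first is that a second value exists only after Level 2 or Level 3 referral: the SAE form records haemoglobin too. The second is that the Revision History contradicts the endpoint list: the deleted endpoints were different ones, and the log matters here only for its statement about data collection. The third is that a comparison between regimens or with S1.EE3 is planned: Section 9.2 plans only a tabulation by regimen.

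**Conclusion.** The point holds in limited form. S2.EE1 needs a measurement that Stage 2 does not routinely make, and the SAP does not settle how patients without it are counted. Read literally, Section 8 gives a proportion in a selected subset that overstates risk. With all treated patients as denominator, the result is a lower bound. The confidence interval covers neither problem.

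The size in this trial cannot be known from the SAP. The 10-fold and 33-fold figures only restate assumed re-tested shares of 10% and 3%, so they are not evidence of how large the discrepancy will be. The conclusion rests on the Revision History's statement about haemoglobin collection and on the inference that re-testing follows symptoms. It warrants correction before analysis but does not touch the primary or secondary endpoints.

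**What to change.** Choose one of the following.

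1. Delete S2.EE1 from Sections 2.2.2 and 9.2, on the reason version 9.0 already gives for the two sister endpoints.
2. Redefine it as the number of patients with a detected haemoglobin fall of more than 25% to below 7 g/dl.

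If a proportion is kept:
- exempt S2.EE1 from the available-case rule in Section 8;
- report it per all primaquine-treated patients and label it a minimum;
- show beside it, for each regimen, the number of patients with a follow-up haemoglobin;
- state that it does not support comparison between regimens or with S1.EE3, since Stage 1 had reviews on days 3 and 7 with haemoglobin results analysed at both.

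The cost is SAP wording and one extra table row. No new data are needed. What is given up is the claim to estimate a rate: the result becomes a minimum count.

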## 3 Study Methods

### 3.1 Study design

This is a staged, multicentre, implementation, before-and-after study of a revised case management package for patients with vivax malaria presenting to community health facilities in Indonesia and Papua New Guinea.

The study will be conducted at 10 pre-existing health facilities, 4 in Papua New Guinea (two in stage 1) and 6 in Indonesia (two in stage 1), all of which have significant experience managing patients with vivax malaria.

All of the study health facilities will collect surveillance data that are reported as part of national malaria surveillance systems. These data include patient demographics, diagnosis and treatment. Prior to the start of the project, selected sites have undergone several rounds of continuous quality improvement (CQI) to improve the quality of data collection. Further enhancements to malariometric surveillance and pharmacovigilance will be made as part of the revised case management with a plan to roll these changes out on a wider scale if the changes prove feasible and cost-effective.

The study will be divided into multiple stages (Figure 1). Prior to commencement of Stage 1, enhanced continuous malariometric surveillance and pharmacovigilance will be established at all 10 health facilities. These systems have already been established in 4 sites in PNG and 4 in Papua with more

than 12 months of data available. Similar surveillance systems will also be established in North Sumatra and Lampung.

Within the first three months of the SCOPE pre-implementation period, in-depth interviews with key stakeholders and community surveys will be conducted to determine the acceptability, operational feasibility, performance and costs of existing vivax malaria management strategies, as well as baseline *P. vivax* slide or RDT positivity rates. Qualitative, economic and clinical data collection will not necessarily happen simultaneously.

Midway through the Pre-Implementation Stage, consecutive patients (within the bounds of participant accrual limits) presenting to each health facility with fever will be asked to participate in the Pre-Implementation Survey aiming for a total of 200 patients at each facility. Informed consent and assent for participation will be requested. A repeat cross-sectional survey of 200 consecutive patients presenting to each health facility with fever will then be conducted in the final 6 months of the post-implementation period for comparative purposes.

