### 3.1.1. Stage 1 – Preliminary safety and feasibility study

In Stage 1, the feasibility, safety and tolerability of point-of-care G6PD testing and PQ7 in G6PD normal (>70%) patients will be determined in 4 selected health facilities with staff undertaking clinical review on day 3 and also day 7 to ensure patient safety. Stage 2 will only proceed after review of the Stage 1 data by SRT and SMC.

After 3 months, the revised case management will be rolled out at 4 selected sites (2 in Indonesia and 2 in PNG), initiating Stage 1. The remaining sites will continue the Pre-Implementation Stage. Stage 1 is anticipated to last 6 months, during which a total of 800 patients with *P. vivax* malaria (~500 from Indonesia and ~300 from PNG) will be treated (Figure 1).

All patients that are eligible for and consent to participate in the study, will be tested by quantitative G6PD activity assessment using the G6PD STANDARD (SD biosensor, ROK). Patients with G6PD activity >70% ( $\geq 6.1$  U/gHb) will be prescribed primaquine at a total dose of 7 mg/kg over 7 days (PQ7) and those with 30-70% activity (4.1-6.0 U/gHb) will be prescribed the same total dose of primaquine over 14 days (PQ14). Patients with G6PD activity <30% ( $\leq 4.0$  U/gHb) will be prescribed primaquine at a dose of 0.75 mg/kg/week for 8 weeks (PQ8w).

The safety review team (SRT) will review all AESI (adverse event of special interest) and SAE (severe adverse event) data after every 100 patients treated with primaquine and may request to review additional data if there are safety concerns. A formal interim analysis is planned after enrolment of 400 patients (~150 patients from PNG, ~250 patient from Indonesia). The SRT will review the interim analysis outputs and share with the Safety Monitoring Committee (SMC) who will conduct an interim review and issue a recommendation regarding continuation of Stage 1.

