The model will include time (month) as a continuous variable, a binary variable for the implementation intervention (see (a) and (b) above), an interaction between elapsed time (since implementation) and the implementation, seasonal variation in malaria (captured using splines), adjusted for potential time-varying confounding variables including large scale malaria control activities outside of the SCOPE study and unexpected antimalarial stock outages, and allowing for a random effect for intercept to account for clustering by health facility site (Turner SL et al. 2021).

For the effectiveness outcome S2.SE15, monthly incidence of symptomatic *P. vivax* malaria will be calculated using clinic catchment populations provided by health facilities (or if not available, the most recent census). Incidence rate ratios (IRRs) (95% CIs) for the intervention effect will be estimated from a negative binomial regression model fitted to the monthly aggregated data.

**Figure 2.** Example impact model for the implementation package on the effectiveness outcome measure S2.SE15 (incidence of symptomatic *P. vivax* malaria infections). An impact model with an immediate change in level and slope. While immediate level change is allowed to occur in this model at the time of implementation, the estimand of interest with regards to level change will be calculated 6 months after implementation (at 12 months) relative to the implementation timepoint (at 6 months).

[figure not shown]

For comparison of outcomes S2.SE16 (the proportion of febrile patients with asexual *P. vivax* parasitaemia by microscopy) and S2.SE14 (the proportion of patients with severe anaemia (haemoglobin < 7 g/dl), determined from cross-sectional surveys in the pre- and post-implementation periods), prevalence ratios (95% CIs) for the intervention effect will be estimated from log-binomial regression models, and if there are convergence issues, Poisson regression with robust variance will be performed (Barros AJD & Hirakata VN 2003).

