## 9.3 Measures to Adjust for Confounders, Heterogeneity and Autocorrelation

### Confounders

Both pre- and post-implementation surveillance periods will be of sufficient duration to minimise the risk of outlier seasonal and social events on the incidence of vivax malaria. Multivariable models, controlling for known potential confounders such as sex, age, weight, calendar month and seasonality will be used for comparisons of malaria incidence, slide positivity and other indices. For the exploratory outcomes, S1.EE1 and S1.EE2 multivariable linear regression models will be adjusted for known potential confounders, baseline haemoglobin levels and G6PD enzyme activity level.

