## SENSITIVITY ANALYSIS - Pools Stage 1 and Stage 2 and includes the one month downtime in between

[figure not shown]

**Figure 2: Pre- and post-implementation periods for S2.SO15 sensitivity analysis displayed by areas with shading. This includes stage 1 & 2 implementation within the post-implementation period as seen with areas of orange and green with shading overlay. The pre-implementation period for each health facility is shown by the shaded pink area.**

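### The before and after fever surveys (S2.SE14, S2.SE16) are timed by study stage with no calendar-month matching, and the planned seasonal adjustment can only weakly separate season from period

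*SAP*

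**What the plan says.** SAP Section 3.1 sets both surveys by study stage. The first: "Midway through the Pre-Implementation Stage, consecutive patients (within the bounds of participant accrual limits) presenting to each health facility with fever", aiming for 200 patients per facility. The repeat survey of 200 per facility "will then be conducted in the final 6 months of the post-implementation period for comparative purposes". No rule in the SAP ties the months of the second survey to those of the first.

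The stages differ by facility. Section 3.1.1 says "After 3 months, the revised case management will be rolled out at 4 selected sites", "The remaining sites will continue the Pre-Implementation Stage" and "Stage 1 is anticipated to last 6 months". The sensitivity analysis in Appendix 4 "includes the one month downtime in between", that is, between Stages 1 and 2. Section 3.1.2 requires at least 12 months of surveillance before and at least 12 months after implementation.

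For the analysis of S2.SE14 and S2.SE16, Section 9.2 says "prevalence ratios (95% CIs) for the intervention effect will be estimated from log-binomial regression models", with robust Poisson regression as the fallback. It names no covariates. Section 9.3 (Confounders) makes a general statement that multivariable models controlling for sex, age, weight, "calendar month and seasonality will be used for comparisons of malaria incidence, slide positivity and other indices". Section 7 lists covariates for safety outcomes and for patient-level effectiveness outcomes, and season is in neither list.

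**The concern.** The SAP treats season as a real confounder in its other effectiveness comparisons. It plans seasonal splines for S2.SE15, S2.SE17 and S2.SE18, and a rainy/dry sensitivity analysis for S2.SE15. The survey comparison is more exposed than these, because each facility supplies two short snapshots instead of a continuous series. If a facility's snapshots fall in different seasons, its before-after difference contains a seasonal change as well as any package effect. The direction depends on which survey lands in the higher season, so the bias could favour the package or hide a benefit.

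The prevalence ratios that answer S2.SO14 and S2.SO16 are at stake. They are secondary objectives, but these surveys are their only stated data source.

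**Working it through.** **Stated figure.** Section 6.2 gives 4,000 survey patients in total: 200 × 10 facilities × 2 surveys = 4,000, which reproduces. The SAP gives no power or precision figure for S2.SE14 or S2.SE16.

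**Calendar.** Count months from the start of pre-implementation.
- Stage 2 starts at 3 + 6 + 1 = month 10.
- With 12 months of Stage 2, the final six months are months 16 to 22.
- Stage 1 facilities have a 3-month pre-implementation period, so midway is month 1.5. The other six stay in pre-implementation to month 10, so midway is month 5.

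The seasonal offset is the gap between surveys modulo 12, taken the shorter way round the year.
- Stage 1 facilities: at month 16, 14.5 − 12 = 2.5; at month 19.5, 18 − 12 = 6; at month 22, 20.5 − 12 = 8.5, which is 3.5 the shorter way. The range is 2.5 to 6 months. From month 16.5 onward, 5.5/6 = 92% of the window, the offset is 3 months or more.
- Other six: at month 16, 11, which is 1 the shorter way; at month 17, exactly 12, so 0; at month 22, 17 − 12 = 5. The range is 0 to 5 months, and 2/6 (a third) of the window is 3 months or more away.
- If the other six have a 12-month pre-implementation period: midway is month 6, the window is months 18 to 24, and the range is 0 to 6 months.

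**Sensitivity to the gap between stages** (0, 3 and 6 months are assumptions):

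| Gap (months) | Stage 1 facilities | Other six |
|---|---|---|
| 0 | 1.5 to 6.0 | 0 to 4.5 |
| 1 | 2.5 to 6.0 | 0 to 5.0 |
| 3 | 1.5 to 6.0 | 0 to 6.0 |
| 6 | 0 to 4.5 | 1.5 to 6.0 |

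**Length of a survey.** If every P. vivax episode in Section 4.2.1, Table 1 presents with fever and takes part, the days to reach 200 are at most 200/(annual episodes/365). At the four Timika facilities this gives 15 (4,937 episodes), 20 (3,681), 23 (3,173) and 63 (1,164) days. At the other six it gives 53 to 177 days. Accrual limits could lengthen these, but at the busiest facilities a survey is a snapshot within one season.

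**Size if season is not adjusted for.** The documents give neither seasonal amplitude nor prevalence. Assume an annual sinusoid on the log scale with peak-to-trough ratio R, no package effect, the worst phase, and the same shift at every facility. The prevalence ratio at offset d months is then R^(−sin(πd/12)).

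| Offset | R = 1.25 | R = 1.5 | R = 2.0 |
|---|---|---|---|
| 2.5 months (sin = 0.609) | 0.87 | 0.78 | 0.66 |
| 3 months (sin = 0.707) | 0.85 | 0.75 | 0.61 |
| 6 months (sin = 1) | 0.80 | 0.67 | 0.50 |

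With the phase reversed, the ratios are the reciprocals. With 2,000 patients per period, two-sided alpha 0.05 and clustering ignored, the chance of a falsely significant result at a 3-month offset is 38%, 86% and over 99% at 10% prevalence, and 70%, over 99% and over 99% at 20%.

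**What adjustment achieves.** Take facility effects, a period effect and one annual harmonic per country, with 20% prevalence, two assumed Stage 1 facilities in each country, and survey lengths of half the upper limits above. Without season, the standard error of the log prevalence ratio is √(2 × 0.8/(0.2 × 2,000)) = 0.063. With season:
- First surveys at each facility's own midpoint: 0.166 if all repeat surveys are mid-window, 0.148 if staggered across it (variance 6.9 and 5.5 times larger).
- First surveys all at month 5: 0.149 and 0.098 (5.5 and 2.4 times larger).

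The period effect is estimable in all four layouts, but the estimate depends on the assumed seasonal shape.

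**The case against.** The strongest reply is that the SAP already plans for season. Section 9.3 promises control for calendar month and seasonality, and slide positivity is S2.SE16 in substance. An adjusted interval would widen to reflect the lost information, and random facility effects, one of the options in Section 9.2, would keep some between-facility information that fixed effects discard. This stands. It rules out a stronger reading that a reader might infer: that seasonal change will simply be reported as the package effect, or that the two can never be separated. The unadjusted ratios above show what is at risk if the Section 9.2 model is fitted as written; they do not predict the planned result. What Section 9.3 leaves open is the form of the terms, and severe anaemia is covered only by its closing catch-all.

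Second, the calendar is not firm. The length of Stage 1 is an anticipated one, Section 4.2 records slower recruitment than expected, the 12-month periods are minimums, and Figure 1, which may show survey months, is not available here. This also stands. It would be wrong to infer that all ten facilities are out of season by design: on the stated calendar the other six can match exactly, and a longer gap would let the Stage 1 facilities match.

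Third, the amplitude is assumed, a common shift across two countries is a worst case, and the SAP says nothing about seasonality of severe anaemia. The size is therefore open. The missing matching rule is not.

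Finally, a late window is reasonable for an effect that builds over time. Matching months inside that window does not conflict with it.

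**Conclusion.** The concern holds in a limited form. The survey rule permits a before-after comparison across different seasons. On the stated 3 + 6 + 1 + 12 month calendar it gives offsets of 2.5 to 6 months at the four Stage 1 facilities and allows 0 to 5 months at the other six (0 to 6 with a 12-month pre-implementation period). Adjustment is promised in general terms but not carried into the survey models. In the layouts tried it costs a 2.4- to 6.9-fold rise in variance and leaves the estimate dependent on the chosen seasonal curve.

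The size of any bias cannot be taken from the documents. For scale only, the fall in incidence predicted in Section 4.2.1 at 70% recruitment is 17.11/135.8 = 12.6%, a ratio of 0.87. An unadjusted 2.5-month offset with an assumed peak-to-trough ratio of 1.25 gives the same ratio. That prediction concerns clinic case counts, not prevalence among febrile patients, so the comparison is only indicative.

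**What to change.** - **Section 3.1:** require each facility's post-implementation survey to run in the same calendar month(s) as its pre-implementation survey (±1 month) where the final-six-month window allows, and otherwise as close as the window allows.
- **Section 9.2:** write the seasonal terms promised in Section 9.3 into the S2.SE14 and S2.SE16 models, stating their form.
- **Appendix 3:** tabulate both survey dates by facility, for example alongside Table 8.
- **Section 10:** add a sensitivity analysis of S2.SE14 and S2.SE16 limited to facilities whose surveys match within ±1 month. Keep the all-facility estimate as the main one: on the stated calendar the restriction would drop all four Stage 1 facilities, including two of the four in PNG.

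If the surveys are already complete, only the last three changes apply, and they should be fixed before the survey results are examined.

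The cost is one scheduling rule, a model specification, one table and one sensitivity analysis. The downside is less freedom in scheduling and wider intervals in the adjusted and restricted analyses.
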